## Background

### Background and rationale

Dental caries, the most prevalent oral disease, is still a major health issue worldwide (1). This multifactorial dynamic disease results in mineral loss of dental structure, is dental-biofilm-mediated, and can be modulated by diet (2). In children, it can affect their mastication function, alongside their smile and manner of speaking, and can be a significant blow to their oral health-related quality of life (3).

Children in mixed dentition, which usually begins at six years of age with the eruption of the first permanent tooth and continues until the exfoliation of the last primary tooth at around 12 years of age, are highly at risk for dental caries (4). This is mainly because teeth are most prone to caries in the first 2–4 years of eruption (5). Moreover, erupting teeth are out of alignment with their adjacent teeth and the gingiva in mixed dentition is sensitive and tender, making dental hygiene a challenge for children and their parents (4).

Contrary to the common belief that the rate of dental caries has declined in industrialized countries, this disease is still highly prevalent in these countries (6). It is believed that in European countries, 61% of 6- to 12-year-old children have experienced dental caries (7). A systematic review recently pointed out that the prevalence of dental caries has increased over the past few years in countries from the Middle East and North Africa region (6). So, it is evident that there is a great need for preventive interventions to decrease caries prevalence in children worldwide.

A rather novel preventive method is the usage of probiotics, which seems to be quite effective in controlling dental caries (8). Probiotics are “live microorganisms that confer a health benefit on the host when administered in adequate amounts” (9). Throughout the years, several studies have evaluated the effects of probiotics on oral health and stated that probiotics can reduce the numbers of pathogenic microorganisms, replace them (10, 11), and prevent or treat oral candidiasis, periodontitis, gingivitis, and halitosis (12, 13). Additionally, previous studies indicated the capability of probiotics to enhance the oral immune system and increase salivary Immunoglobulin A (IgA) secretion (14, 15).

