### Eligibility criteria

The inclusion criteria will be as followed: healthy, 6- to 12-year-old children, during the mixed dentition, no active or untreated carious lesions, no severe crowding, no marked inflammation in oral cavity.

The exclusion criteria will be the presence of any inflammatory disease and use of any medications, supplements, or probiotic intake within the last two weeks or during the intervention. The patients who fail to follow-up will also be excluded from the study.

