### Study product and intervention

The postbiotic strain *Bifidobacterium animalis subsp. animalis* PTCC1631 will be used. The intervention will be in form of a postbiotic-toothpaste (*B. animalis subsp. animalis, 10*^*9*^^*CFU*^/*g* (22)). The postbiotic strain was ordered from the Persian Type Culture Collection center, a subset of the Iranian Research Organization for Science and Technology. The postbiotic and placebo-toothpaste are similar in packaging, color, taste, and scent, and the only difference is the absence of the postbiotic ingredient in the placebo-toothpaste. Table 1 shows the ingredients of the toothpastes.

**Table 1 T1:** List of the ingredients of each toothpaste.

	Postbiotic-toothpaste (100 gr)	Placebo-toothpaste (100 gr)
*B. animalis subsp. animalis*	1–5 gr	
Sorbitol	30–40 gr	30–40 gr
Glycerin	20–30 gr	20–30 gr
Calcium carbonate	15–25	15–25
Carboxy methyl cellulose	1–2 gr	1–2 gr
Sodium saccharin	0.1–0.5 gr	0.1–0.5 gr
Sodium lauryl ether sulfate	2–5 gr	2–5 gr
Strawberry flavor	1–2 gr	1–2 gr
Distilled water	qs to 21 ml	qs to 21 ml

Eligible participants will be randomly allocated to two groups, intervention and control. The postbiotic-toothpaste will be given to the children in the intervention group and the children in the control group will receive the placebo-toothpaste. Children in both groups will be asked to brush their teeth twice a day (in the morning and at night) for two minutes, under the supervision of their parents, for four weeks. To eliminate any possible confounding effect of the method of tooth-brushing on the results, children and their parents will be instructed on how, when, and how long to brush their teeth at the beginning of the study.

In order to ensure participants adherence, parents will receive a message on a weekly basis to remind them the importance of tooth-brushing twice a day. Also, to motivate and encourage the children, they will be asked to record daily short videos of themselves while brushing their teeth and put it all together at the end of the four weeks.

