### Outcomes

The primary outcome of this study will be the salivary IgA levels of the children and will be reported in mg/100ml. The secondary outcome will be the pH levels of saliva in children. The primary and secondary outcomes will be assessed at the baseline, before any intervention, and after four weeks of intervention.

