### Data collection

At the beginning of the study, demographic information (age and gender), medical history, accompanying medication, and any usage of antibiotics and probiotics will be recorded. The eligible subjects will be told not to eat or drink anything for one hour before the saliva collection. Afterwards, one ml of the unstimulated whole saliva of children will be collected into sterilized plastic test tubes using the spitting method between 9.00 and 12.00 a.m. under controlled temperature (23°C). The saliva samples will be kept at −80°C until they are sent to laboratory, where the levels of salivary IgA will be determined with enzyme-linked immunosorbent assay (ELISA) previously described in detail by Sonesson et al. (24). The 96 well-plates will be coated overnight by anti-human *α*-chain-specific IgA. The next day, the wells will be washed with Phosphate-Buffered Saline (PBS) containing 0.05% Tween-20 and blocked by 1% Bovine Serum Albumin (BSA) at 37°C for 1 h. Diluted saliva samples and standards will be incubated in wells for 1 h at 37°C. The wells will be washed and biotinylated anti-human IgA antibody will be added. After washing away unbound biotinylated antibody, HRP-conjugated streptavidin will be pipetted to the wells. The wells will again be washed, a TMB substrate solution will be added to the wells and color develops in proportion to the amount of IgA bound. The Stop Solution will change the color from blue to yellow, and the intensity of the color will be measured at 450 nm. The results will be plotted against a standard curve and multiplied with the dilution factor. Immediately after sample collection in order to prevent degradation of the saliva, pH analysis will be carried out using portable pH meter (Hanna Instruments®, HI98191, RI, United States) which will be calibrated with distilled water for each time of use. At the follow-up session, outcomes will be reevaluated accordingly. A trained pediatric dentist will collect all the data. Figure 2 presents schedule of enrolment, intervention, and assessments.

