### Statistical analysis

The analysis of the data will be based on the intention-to-treat analysis and all recruited participants will be considered. Data normality will be examined using the Kolmogorov-Smirnov test. The variables will be reported as mean ± SD or median. The percentage changes for each variable will be calculated using the following formula in which *E* and *B* stand for the end value and the baseline value of the variable, respectively.

$$\left[\;\frac{E-B}{B\;\times \;100}\;\right]$$

In case of meeting the assumption of normality, the significant changes between the two groups will be evaluated using the independent t-test, otherwise, Mann-Whitney analysis will be used. Comparison of the mean of variables at baseline with that of post-intervention within each group will be conducted using paired *t*-test or Wilcoxon signed-rank test. In order to control any possible confounding variable, the analysis of covariance (ANCOVA) will be used when necessary.

All analyses will be performed using the Statistical Package for Social Sciences, version 22.0 (SPSS, Inc., Chicago, IL, United States) with statistical significance at *p *< 0.05.

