### Adverse events

Since the study product will be in form of a toothpaste, minimal harm is expected. However, an adverse event (AE) has been defined as any unfavorable discomfort in the mouth during the study period. All the children and their parents will be advised to report any AE immediately and in case of AE, participant(s) will be excluded from the study.

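### Excluding every child who reports mouth discomfort conflicts, as written, with the promised intention-to-treat analysis and creates avoidable missing week-4 outcomes

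*Protocol article*

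**What the plan says.** The Adverse events section gives the definition: "an adverse event (AE) has been defined as any unfavorable discomfort in the mouth during the study period". It sets no threshold for severity, duration or relation to the paste. The consequence is equally unconditional: "in case of AE, participant(s) will be excluded from the study".

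The Statistical analysis section commits to intention-to-treat and adds that "all recruited participants will be considered".

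On timing, the Outcomes section says: "The primary and secondary outcomes will be assessed at the baseline, before any intervention, and after four weeks of intervention". The Data collection section agrees, with a single later session: "At the follow-up session, outcomes will be reevaluated accordingly".

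The Eligibility criteria section uses the same expression for children lost to follow-up: "The patients who fail to follow-up will also be excluded from the study".

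Of the two pastes, the Study product and intervention section says that "the only difference is the absence of the postbiotic ingredient in the placebo-toothpaste".

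**The concern.** Recording every complaint of discomfort is right, and stopping the paste can be a sensible precaution. The fault is removing the child from the study. The event happens after randomisation and may depend on which paste the child received. Because IgA and pH are measured only at baseline and week 4, a child removed in between contributes no observed change. The conduct rule and the analysis commitment therefore cannot both be carried out as written.

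The main risk is bias. The pastes differ only in the postbiotic, so if that ingredient causes discomfort, more children leave the active arm. The children compared at week 4 are then no longer the groups that were randomised. The comparison is biased if the excluded children would also have had a different IgA change.

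The rule may also reach further than intended. All participants are in mixed dentition, and the Background says that "the gingiva in mixed dentition is sensitive and tender". Read literally, discomfort from an erupting or loose tooth would trigger exclusion. That is an inference with no rate behind it. It bears on how many children are lost, not on whether the loss differs between arms.

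**Working it through.** **Inputs from the Sample size section.** Means 1.4 and −3.1, so a planned difference of 1.4 − (−3.1) = 4.5; SDs 4.1 and 5.9; α = 0.05 two-sided; β = 0.1; losses up to 30%; 40 per arm. I read the means as changes from baseline, since one is negative.

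**The plan's own figure.** n = (1.2816 + 1.9600)² × (4.1² + 5.9²) / 4.5² = 10.508 × 51.62 / 20.25 = 26.8, so 27 per arm. Then 27 / 0.7 = 38.6, or 39. A t-based calculation gives 28, and 28 / 0.7 = 40. The stated 40 per arm is reproduced.

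**Loss of numbers.** The 30% allowance is 0.30 × 40 = 12 per arm, leaving 28. Power of the Welch t-test (noncentral t) at a difference of 4.5:

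| Children per arm | Power |
|---|---|
| 40 (no loss) | 0.974 |
| 36 (10% excluded) | 0.959 |
| 28 (all 12 losses used) | 0.901 |

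Losses that are equal between arms and unrelated to IgA are therefore largely absorbed.

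**Selective loss.** Let q be the extra share of the active arm excluded, and D the amount by which their mean IgA change differs from that of the rest of the arm. The whole-arm mean is (1 − q) × (mean of those remaining) + q × (mean of those excluded). Analysing only those remaining shifts the estimate by q × D. The documents give neither q nor D, so these are assumptions:

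| q | D | Shift q × D | Share of 4.5 |
|---|---|---|---|
| 0.05 | 2.25 | 0.11 | 2.5% |
| 0.10 | 2.25 | 0.23 | 5% |
| 0.20 | 2.25 | 0.45 | 10% |
| 0.20 | 4.5 | 0.90 | 20% |
| any | 0 | 0 | 0% |

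Here 2.25 is half the planned difference. For scale, the standard error of the difference at 40 per arm is √(51.62 / 40) = 1.14, so shifts of 0.11 to 0.45 are about 0.1 to 0.4 standard errors, and 0.90 is about 0.8.

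**Keeping the children in.** Suppose a share q of the active arm stops the paste, gets no benefit at all, and is still sampled. The expected difference is 4.5 × (1 − q):

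| q | Difference | Power, 40 per arm | Power, 28 per arm |
|---|---|---|---|
| 0.05 | 4.28 | 0.960 | 0.870 |
| 0.10 | 4.05 | 0.940 | 0.832 |
| 0.20 | 3.60 | 0.878 | 0.738 |

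This scenario is the D = 4.5 case seen from the other side. Excluding the same children would leave the estimate at 4.5 and overstate the intention-to-treat effect by 4.5 × q, that is 0.23, 0.45 or 0.90. For other reasons why D might differ from zero, the direction cannot be stated in advance.

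**The case against.** The strongest reply is that the text never says in words that sampling stops. Being excluded could mean only that the paste is withdrawn. The follow-up rule is an imperfect parallel, because a child who fails follow-up has no sample by definition, whereas a child with discomfort could still attend. The article is also condensed, and a fuller withdrawal procedure may exist elsewhere. These points limit certainty. But the rule removes the child from the study, not from treatment, and it is unconditional. Staff who follow it literally would not take the sample. If something milder was meant, the sentence still needs correcting.

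The second reply is that nothing in the documents shows material bias. That would need discomfort before week 4, more of it in the active arm, and a different IgA response in those children. The protocol expects minimal harm, children with marked oral inflammation are not eligible, and irritation from shared ingredients should fall on both arms. This stands: the size is hypothetical and, under moderate assumptions, small. Tooth-eruption discomfort likewise should not differ by arm and adds nothing to the case for bias.

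A third reply, that missing-data handling belongs in the analysis plan, does not meet the point. How missing values are analysed is not at issue here. The stated rule itself creates them.

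**Conclusion.** The concern holds. Taken at its natural meaning, the adverse-event rule is incompatible with an intention-to-treat analysis of everyone recruited, because it discards outcomes that could be collected at a session already planned. The conclusion rests on reading exclusion from the study as no week-4 sample, which is the plain sense but is not spelled out.

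The size is uncertain. Under assumed excess exclusions of 5% to 20% in the active arm the bias is 2.5% to 10% of the planned difference, and 20% at the extreme considered. It is zero if the excluded children respond like the others. Loss of power is not the main problem. The sponsor should correct this, because the loss is avoidable and the correction is cheap; it is not a fatal defect.

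**What to change.** Keep the broad definition for recording, and replace the exclusion clause in the Adverse events section with:

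> All mouth discomfort is recorded. The paste may be stopped when the parent or the dentist, blind to arm, judges it necessary. The child stays in follow-up unless consent is withdrawn, gives the week-4 saliva sample, and is analysed in the randomised group.

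Unblinding for serious events and review by the Data Monitoring Committee stay as they are.

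The change is one sentence and adds no visit. The price is dilution if children who stop the paste lose its benefit. In the worst case considered (20% of the active arm with no benefit), power is 0.878 at 40 per arm, and 0.738 if all 12 allowed losses per arm also occur. That diluted effect is the one the stated intention-to-treat analysis is meant to estimate.

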## Discussion

Existing literature indicates that postbiotics have advantageous effects on the human body. They have been proven to be effective in preventing diarrhea, acute gastroenteritis, pharyngitis, and laryngitis (24), and reducing respiratory tract infection in children (25). Numerous *in vitro* and *in vivo* studies have also shown the immunomodulatory effects of postbiotics, such as enhancing anti-inflammatory cytokines production (26), inhibiting tumor necrosis factor (TNF-*α*) secretion (27), and promoting T helper one immune response (28). In addition, probiotics and fermented foods supplementation significantly increased salivary IgA secretion rate (15). There have been few studies, however, that evaluated the influence of postbiotics on the secretion of salivary IgA.

Hishiki et al. in 2020 evaluated the effect of a heat-killed probiotic strain on viral infection of the respiratory tract in 3- to 6-year-old children and stated that after four months of intervention, the levels of secretory IgA in saliva were higher in the postbiotic group than that of the placebo group. Although, the results were not significant (29).

In another study in 2021, Lin et al. compared the effect of viable and heat-killed probiotic strains on oral immunity and found that after four weeks of viable and heat-killed probiotic administration, salivary IgA levels significantly increased in both groups (14).

In 2022, Lin et al. evaluated the effects of heat-killed probiotics and postbiotics on oral health and concluded that after four weeks of intervention, the levels of salivary IgA increased in both groups, and postbiotic supplementation can improve oral immunity (30).

Considering the shortage of clinical studies on the administration of postbiotics to increase oral immunity in children, through this randomized controlled trial, we propose to inspect the effect of postbiotics on children's oral immunity. If postbiotics-toothpaste prove to be effective in enhancing the oral immunity of children, they can be used as a new prophylactic method to prevent dental caries and other oral diseases. We expect the result of this study to be of great help to researchers working on the immunomodulatory effects of postbiotics in children.
